# The role of Erzhi Tiangui formula in expected poor ovarian responders undergoing in vitro fertilization-embryo transfer: A multicenter, randomized, double-blind, placebo-controlled trial

**DOI:** 10.1097/MD.0000000000034088

**Published:** 2023-07-07

**Keywords:** Chinese medicine, Erzhi Tiangui formula, IVF-ET, poor ovarian response, study protocol

## Abstract

**Method::**

The study is a multicenter, double-blind, placebo-controlled, randomized controlled trial (RCT), which will be conducted at 10 reproductive centers of tertiary hospitals. This study will enroll 480 women with expected POR of advanced age (≥35 years old) who fulfill the 2011 Bologna criteria. Participants will be assigned to either the EZTG group or the placebo group at random in an equal ratio. Each individual will receive conventional IVF-ET with EZTG granules or placebo as a complementary treatment. The primary outcome is the number of oocytes retrieved. Adverse events and safety assessments will be also conducted.

**Discussion::**

This study aims to provide robust evidence of the efficacy and safety of EZTG formula as a complementary treatment for advanced-age women with expected POR undergoing IVF-ET.

## 1. Introduction

The postponement of childbearing has become a global trend, which led to a gradual increase in the proportion of infertile women of advanced age. In women older than 35 years old, ovarian reserve and oocyte quality are diminished, making assisted reproductive technology (ART) more likely to be required to achieve pregnancy.^[1–3]^ For women undergoing in vitro fertilization-embryo transfer (IVF-ET), POR to controlled ovarian stimulation (COS) remains a serious dilemma. POR indicates a reduction in follicular response, resulting in a reduced number of retrieved oocytes. And advanced age is considered the most relevant risk factor for POR.^[4]^ POR is generally associated with poor clinical outcomes, including fewer retrieved oocytes, a lower clinical pregnancy rate, and a lower cumulative live birth rate (CLBR),^[5–7]^ which was referred to as “expected poor responders” or “low prognosis patients.”

Several adjuvant treatments before or during IVF-ET have been suggested for the population, such as dehydroepiandrosterone, estradiol, and growth hormone supplementation.^[8–10]^ Nonetheless, the evidence of efficacy is still limited and not satisfying.^[11]^ Traditional Chinese medicine (TCM) is an independent medical system with a rich theoretical basis. According to TCM theory, the “kidney,” also known as “Shen,” is in charge of the body aging and reproductive abilities. The kidney qi and kidney yin can be abstractly summarized as the ability to maintain the functioning of the female reproductive system and the reserve of female fertility, respectively. Therefore, the deficiency of kidney qi and kidney yin will accelerate the aging process and aggravate the loss of fertility, which is analogous to the pathogenesis of diminished ovarian reserve, and POR during IVF. Notably, some studies have indicated the benefit of kidney-tonifying TCM in improving the prognosis of elderly women with POR.^[12–14]^

Erzhi Tiangui (EZTG) formula, with the function of tonifying the kidney-qi and nourishing the kidney-yin, is in the form of granules with ten herbal ingredients. It has been widely applied in reproductive centers for over 20 years and demonstrated benefits as a supplementary treatment during ART and IVF for advanced-age women with expected POR. Some previous studies have indicated the benefits of EZTG on the clinical outcome in the population and explored the mechanism by which EZTG improve the ovarian reserve and quality of oocytes and embryos.^[15–19]^

The complementary and synergistic role of TCM for individuals undergoing IVF is an area that merits further attention and research.^[20,21]^ The present study is a multi-center, double-blinded, placebo-controlled, large-scale, superiority randomized controlled trial (RCT) with a robust methodological design. The purpose of the study is to provide robust clinical evidence that EZTG formula are effective in improving oocyte yield and other clinical outcomes in advanced-age women with expected POR undergoing IVF-ET.

## 2. Methods and analysis

### 2.1. Study design

The study is designed as a multi-center, prospective, randomized, double-blinded, placebo-controlled trial. We recruited participants who are scheduled IVF-ET from reproductive centers in ten tertiary hospitals. The primary study site is the Reproductive Center of Integrated Medicine of the Affiliated Hospital of the Shandong University of TCM. Patient enrollment is scheduled from May 2023 to June 2025. To ensure the consistency of the procedures in all the centers, All participating researchers will be uniformly trained. Regular communication and study visits will be performed at all study sites. In addition, meetings with all study sites will be held annually or more frequently. The study protocol is designed and written based on the SPIRIT checklist.^[22]^ The trial was registered at the National Institutes of Health clinical trials database (ClinicalTrials.gov, ID: NCT05698550). The study flowchart is shown in Figure 1, and the timetable of the study is summarized in Table 1.

**Figure 1. F1:**
[figure not shown]
Flow diagram of participant recruitment (AFC = antral follicle count, EZTG = Erzhi Tiangui, GnRH = gonadotrophin releasing hormone, ICSI = Intracytoplasmic sperm injection, IVF = in vitro fertilization, POR = poor ovarian response).

**Table 1 F3:**
[figure not shown]
Timetable of the study.

### 2.2. Patients recruitment

A total of 480 aged women diagnosed with POR will be included in the study. Potentially eligible patients will be recruited by the clinicians in the reproductive center of ten tertiary hospitals. The detail about the trial will be introduced to them on their first visit. After a wash-out period of at least 2 weeks, eligible women will be arranged a second visit on day 2 or 3 of a menstrual cycle. Then, all couples will provide written informed consent before participation following the approval by the ethics committees of participating reproductive centers. Given the high prevalence of the disease and the large outpatient volume in participating centers, we will not apply other methods of recruitment.

### 2.3. Patient and public involvement

The study protocol was designed without patient or public participation. The randomization, allocation, and treatment procedures will not be interfered with by participants’ preferences. All results of the study will be distributed to participants upon request.

### 2.4. Eligibility criteria

#### 2.4.1. Diagnostic criteria of POR.

The diagnostic criteria of POR are following the ESHRE Bologna criteria,^[4]^ which included: advanced age (>40 years) or any other risk factor for a POR; retrieval of <3 oocytes following previous conventional ovarian stimulation; and reduced ovarian reserve test (antral follicle count [AFC] < 5–7 or anti-Müllerian hormone < 0.5–1.1 ng/mL). Patients who meet at least the above 2 conditions will be diagnosed with POR.

#### 2.4.2. Diagnostic criteria for TCM kidney qi-yin deficiency syndrome differentiation.

Kidney qi-yin deficiency syndrome is associated with the following symptoms:

(1) Heavy menstrual bleeding (>80 mL) or light menstrual bleeding (<5 mL), along with the color of dark red or thin and watery blood; (2) The waist and knees are sour and weak, or pain in the heels; (3) Dizziness, tinnitus, and mental exhaustion; (4) Low sexual desire, less vaginal discharge, and loss of armpit or pubic hair; (5) Typical pulse manifestation: deep and weak pulse in both wrists. The diagnosis of kidney qi-yin deficiency is made if there are 3 or more of the above symptoms, while "Heavy menstrual bleeding (>80 mL) or light menstrual bleeding (<5 mL), along with the color of dark red or thin and watery blood" and "The waist and knees are sour and weak, or pain in the heels" are necessary conditions to fulfill. The syndrome identification will be performed by 2 associate professors independently examining each patient. Participants will be included if the syndrome diagnosis is consistent from both professors.

#### 2.4.3. Inclusion criteria.

Women aged ≥35 years, eligible for IVF or Intracytoplasmic sperm injection treatment.Women who meet the diagnostic criteria for POR.Women who meet the diagnostic criteria for kidney qi-yin deficiency syndrome.

#### 2.4.4. Exclusion criteria.

Women with any of the following exclusion criteria are not eligible to participate in the study:

Women aged ≥ 43 years.Women with body mass index ≥35 kg/m^2^.Women undergoing oocyte donor cycle.Women with a history of recurrent spontaneous abortion or repeated implantation failure, defined as 2 or more spontaneous abortions or failed IVF-ET attempts.Women undergoing a cycle of In vitro Maturation or Preimplantation Genetic Testing.Women with uterine abnormalities, congenital (e.g., bicornuate uterus) or acquired (e.g., severe adenomyosis and multiple endometrial polyps).Women with uterine appendage abnormalities (e.g., non-surgically treated hydrosalpinx and ovarian endometriosis cyst requiring surgery).Unilateral ovarian absence.Women allergic to or intolerant of EZTG or other medications applied in the study.

### 2.5. Dropout and discontinuation criteria

Patients who withdraw from the study voluntarily, who experience poor compliance during the study period, or who are considered not suitable for further participation in the trial by the researcher will be removed from the RCT. The reasons include, but are not limited to the following: Participants do not take EZTG at the prescribed dosage or duration; Participants experience adverse reactions or complications related to EZTG during the study period; Participants are pregnant before IVF cycle; Participants take other medications during the study that may interfere with the study results, such as oral conceptive pills and estradiol. The concurrent use of other TCM preparations will also not be allowed.

The trial will be terminated if there are any of the following conditions: The double-blind design is accidentally disclosed or broken, leading to the failure of the trial; Existing evidence to prove no effect of the drug; The ethics committee identifies ethical issues in the experimental process; The prespecified interim analysis finds the expected difference in efficacy between the groups.

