### 2.6. Randomization, allocation, and blinding

Randomization and allocation will start on day 2 or 3 of the previous menstrual cycle before IVF. Eligible women will be stratified by AFC (<5 or ≥5) and randomized within the 2 strata. All participants will be randomly assigned to either the EZTG group or the placebo group in a 1:1 ratio. Randomization will be completed by software (R 4.0.0, R Foundation for Statistical Computing, Vienna, Austria), and different-sized block groups of 2, 4, 6 will be applied. Random number tables will be provided by statistical professionals not involved in the rest of the study and the number will be sealed into brown envelopes. Then the group allocation will be accomplished by opening envelopes sequentially in the order in which patients were recruited.

A double-blind study design will be applied to enhance the quality of the study evidence. Both medications (EZTG granules and placebo) will be prepared in a manner that they will appear similar in appearance, flavor, and smell. Clinicians and patients will not be able to distinguish the difference between groups. The outcome assessment and data analysis will also be conducted in blinding. When the clinical trial is over, the final blind-break process is performed by authorized researchers.

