#### 2.7.3. COS and oocytes retrieval.

Participants will be assessed again for eligibility on day 2 or 3 of the IVF cycle. The participants will also receive hormonal and ultrasound assessments to ensure the feasibility of COS.

Eligible participants will be administrated COS with a Gonadotrophin-releasing hormone antagonist protocol on day 2 or 3 of the menstrual cycle and given recombinant follicle stimulating hormone (Gonal-F, Merck Serono, Switzerland). The starting dose of rFSH will be in a range between 150–225 IU/day, based on the individual baseline characteristics. The COS process will be individualized, and the follow-up dose of rFSH will be adjusted according to the ovarian response during COS every 2 or 3 days. On day 5 or 6 of the ovarian stimulation, gonadotrophin releasing hormone-antagonist (cetrorelix acetate, Cetrotide; Merck Serono, Germany) will be initiated. When more than 2 follicles are at least 18 mm, 250 mg of recombinant human chorionic gonadotrophin will be administered to trigger the final follicular maturation. After 35 to 37 hours, transvaginal ultrasound-guided aspiration is performed. Intracytoplasmic sperm injection will only be performed in cases of severe male factors of infertility.

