### 2.8. Outcomes

#### 2.8.1. Efficacy outcomes.

The primary outcome is the number of oocytes retrieved per COS cycle.

The following secondary outcomes will also be evaluated as secondary outcomes:

Symptom rating scores of kidney qi-yin deficiency syndrome after treatment (The symptom rating scales is shown in Table 3).Difference in rating scores of kidney qi-yin deficiency syndrome before and after treatment.Average daily dose of gonadotropin per COS cycle.Total gonadotropin dose and duration of ovarian stimulation per COS cycle.Cycle cancelation rate per COS cycle. Cycle cancelation is defined as a cycle canceled before obtaining at least 1 viable embryo for any reason.Good quality embryos rate per embryo. A good quality embryo is defined as an embryo that is graded as 6-cell grade 2 (6CII) or better or blastocyst.Embryo implantation rate per embryo, defined as the number of gestation sacs detected divided by the number of embryos transferred.Clinical pregnancy rate per patient, defined as the number of women with identified clinical pregnancies divided by the number of patients randomized to a specific group. Clinical pregnancy is confirmed when 1 or more gestational sacs are detected on transvaginal ultrasound assessment.Early miscarriage rate per patient, defined as the percentage of participants with loss of a diagnosed clinical pregnancy before 12 weeks gestation to the total patients randomized.CLBR per patient, defined as the proportion of deliveries with at least 1 live birth per started cycle or oocyte aspiration, including all fresh and/or frozen embryo transfers until 1 delivery with a live birth or until all embryos were used (within 1 year after randomization).

**Table 3 T3:** Symptom rating scales of kidney qi-yin deficiency syndrome.

Symptoms	Characteristics and severity of the symptoms	Score
The color and quality of the menstruation	The color of the blood is dark red and the quality is thin and watery	5
	The color of the blood is dark red or the quality is thin and watery	3
	Normal color and quality	0
The waist and knees are sour and powerless, or pain in the heels	Severe discomfort that interferes with daily life	6
	Moderate discomfort	4
	Mild discomfort	2
	No obvious discomfort	0
Dizziness and tinnitus	Severe, occurs constantly and interferes with daily life	6
	Moderate, occurs frequently	4
	Mild, occurs occasionally	2
	Not obvious	0
Mental exhaustion	Severe, occurs constantly and interferes with daily life	6

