#### 2.9.2. Planned data analysis.

Intention-to-treat (ITT) analysis will be used for baseline comparisons and the assessment of the effect of EZTG on the total number of retrieved oocytes per COS cycle, as well as other secondary outcomes. T-test, Wilcoxon rank-sum test, or chi-square test will be used to test for differences. The results will be given as mean (standard deviation), median (interquartile range), or frequency (percentage) according to the type and distribution of the variables. A 2-sided *P* < .05 is considered statistically significant with a confidence interval of 95%. Per protocol analysis will be conducted as a sensitivity analysis, including those patients who completed their randomized treatment. If the ITT results conflict with the per protocol results, we will interpret the study results according to the outcome of the ITT analysis.

In addition, a subgroup analysis will be performed according to AFC strata (<5 or ≥5) using a similar approach to the primary analysis. Multiple imputations will be used to process missing values in the data of this study. All statistical work will be performed on SPSS version 26.0 software (IBM Corporation, Armonk, NY).

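### Section 2.5 takes randomised women out of the trial for events after randomisation, which conflicts with the planned ITT analysis, and nothing in the article keeps them in follow-up

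*Protocol article*

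**What the plan says.** **Removal (2.5).** Women who withdraw, comply poorly or are "considered not suitable for further participation in the trial by the researcher will be removed from the RCT". The reasons given, in a list stated to be open-ended, include:
- non-adherence: "Participants do not take EZTG at the prescribed dosage or duration"
- a reaction or complication attributed to the granules
- conception ahead of treatment: "Participants are pregnant before IVF cycle"
- use of other medication that could interfere with the results.

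**Timing (2.6, 2.7).** "Randomization and allocation will start on day 2 or 3 of the previous menstrual cycle before IVF", and the granules start in that same cycle. There is a further check later: "Participants will be assessed again for eligibility on day 2 or 3 of the IVF cycle". Only women who pass it go on to stimulation.

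**Analysis (2.9.2).** "Intention-to-treat (ITT) analysis will be used for baseline comparisons and the assessment of the effect of EZTG" on the primary and secondary outcomes. Per protocol, meaning women who completed their assigned treatment, is a sensitivity analysis, and ITT prevails if the two disagree. Missing values are multiply imputed.

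**Outcomes and follow-up (2.8, 2.10).** The primary outcome is oocytes retrieved per stimulation cycle. Clinical pregnancy is "divided by the number of patients randomized to a specific group", and early miscarriage also uses all randomised women as its denominator. Adverse events are recorded at every visit, and laboratory safety tests are done at baseline and on the trigger day. Follow-up runs to one year after randomisation, or until a live birth or the use of all embryos.

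**The concern.** An ITT analysis needs every randomised woman followed and analysed in her arm, whatever she did with the granules. Section 2.5 instead takes women out of the trial, not merely off treatment, for events that the treatment itself could influence: adherence, tolerability and conception.

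Three results are exposed if centres follow 2.5 literally.
- **Primary outcome.** The observed data would come mainly from adherent, tolerant women. The contrast between ITT and per protocol would then lose most of its meaning, with imputation standing in for counts that could have been collected.
- **Pregnancy.** A conception in the treated cycle before IVF is a possible benefit. A removed woman stays in the all-randomised denominator, while her pregnancy may never reach the numerator.
- **Safety.** The reaction that prompts removal can be recorded, but the trigger-day tests and later events may be missed in those women.

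**Working it through.** **1. The plan's own figure.** Inputs from 2.9.1: difference 1 oocyte, SD 3, two-sided 5%, power 90%, dropout 20%, 240 per arm.

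n per arm = 2 × SD² × (1.960 + 1.282)² / difference² = 2 × 9 × 10.51 / 1 = 189.1, so 190. Then 190 / 0.80 = 237.5, so 238 per arm and 476 in total. With the t distribution: 191, then 239 per arm and 478 in total. The stated 480 reproduces.

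The allowance is 240 × 0.20 = 48 women per arm without a primary outcome, leaving 192. It covers dropout from all causes, so 48 cannot be attributed to the contested reasons alone.

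**2. Power.** Power = Φ(difference / (SD × √(2/n)) − 1.96).
- 192 per arm, difference 1: Φ(1/0.3062 − 1.96) = Φ(1.306) = 90.4%.
- 240 per arm, difference 1: Φ(1/0.2739 − 1.96) = Φ(1.69) = 95.5%.

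Assumption, not in the documents: women now removed are kept, have no benefit, and the SD stays 3. The difference becomes 1 × (1 − share).

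| Share without benefit | Difference | Power, 240 per arm |
|---|---|---|
| 5% | 0.95 | 93.4% |
| 10% | 0.90 | 90.8% |
| 20% | 0.80 | 83.2% |

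**3. Possible bias in the primary comparison if only retained women are compared.** All figures here are assumptions. Under no true effect, let r₁ and r₀ be the shares removed from the EZTG and placebo arms, and let g be the number of oocytes by which removed women would have fallen short of retained women. Bias = (r₁ − r₀) × g. With r₁ = 20% and r₀ = 10%, 192 and 216 women remain, and SE = 3 × √(1/192 + 1/216) = 0.298.

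| g | Bias (oocytes) | Two-sided type I error |
|---|---|---|
| 1 | 0.1 | about 6% |
| 2 | 0.2 | about 10% |
| 3 | 0.3 | about 17% |

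With r₁ = r₀ and the same g in both arms, the bias is 0 and the error stays at 5%. If more women are removed from placebo, the sign reverses.

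**4. Pregnancy rate.** Each uncounted pre-IVF conception lowers its arm's rate by 1/240 = 0.42 percentage points. The documents give no frequency. For illustration, 2% against 1% conceiving before IVF would shift the between-arm difference by 1 point; equal numbers would leave it unchanged.

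**5. The passages side by side.** Sections 2.8.1, 2.9.2 and 2.10 are all built on randomised women. Section 2.5 removes some of them from the trial. No sentence says that removed women are still followed, and none says that their data are discarded.

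**The case against.** The best defence is that removal means only the end of study treatment. Section 2.5 is headed as dropout and discontinuation criteria. Section 2.9.2 commits to ITT, and a per-protocol set of completers presupposes that the ITT set also holds non-completers. Section 2.10 states no exception for removed women. On this reading the fault is one of wording, and analysis-set detail may sit in the full protocol.

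Part of this stands. A reader might infer that the ITT set is really a per-protocol set plus imputed values, that pregnancies on treatment are not counted, or that safety follow-up stops. The article states none of these:
- It never says that removed women's data are discarded.
- Its definition of clinical pregnancy rests on gestational sacs and does not require embryo transfer, so a pre-IVF conception fits it if it is ascertained.
- Adverse events are recorded at visits, and 2.12 requires serious ones to be reported at once.
- A woman pregnant before IVF has no stimulation cycle, so no oocyte count is lost by removing her.
- Removals are decided under blinding. That limits deliberate imbalance, though not imbalance driven by tolerability.

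The defence does not remove the conflict. The wording is removal from the RCT, and it groups non-compliant women with voluntary withdrawals. This is a stated rule that ten centres will apply, not a detail left out. Imputation is a weak substitute: missing at random is doubtful for women removed for non-adherence, a reaction or conception, and many of the outcomes could simply be observed.

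**Conclusion.** The conflict between 2.5 and sections 2.8.1, 2.9.2 and 2.10 is real and needs correcting, because outcomes not collected cannot be recovered later. The accurate claim about consequences is conditional. If 2.5 is followed literally, it can bias the primary and pregnancy comparisons when removals differ between arms, can drop pre-IVF conceptions from the numerator, and can cut short safety follow-up. The documents fix neither size nor direction. The illustrated bias of 0.1 to 0.3 oocytes rests wholly on assumed removal rates and yields, and it is zero if removals are alike in rate and type.

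A reader might also take the 83% power as a flaw in the sample size. It is not. It is the extreme case of the remedy, with one woman in five kept and none of them benefiting; at 5% or 10% the 90% target is still met. The 480 reproduces and stands.

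**What to change.** Reconcile 2.5 with 2.9.2 as follows.
- Separate discontinuation of study treatment from withdrawal of consent for follow-up. When treatment stops is a matter for the investigators and is not at issue here.
- Unless consent for data collection is withdrawn, follow every randomised woman for oocyte count where a stimulation cycle takes place, and for pregnancy, live birth and adverse events. Analyse her in her randomised arm.
- Use the 2.5 reasons only to define the per-protocol set.
- Count pre-IVF conceptions in clinical pregnancy and live birth per randomised woman. The cumulative live birth definition in 2.8.1 is worded per started cycle or aspiration, so it needs matching text.
- State how women without a stimulation cycle, including those pregnant before IVF or failing the second eligibility check, enter the primary analysis.

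The cost is protocol wording, slightly more follow-up data collection and possibly some dilution of the effect, of the size shown in the power table. The planned 480 need not change on this account.

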### 2.9. Statistical analysis

#### 2.9.1. Sample size calculation.

##### 2.9.1.1. Sample size calculation

Sample size calculations referred to previous studies, and the clinical outcomes of aged women with POR from the electronic database in our reproductive center.^[9,23]^ The study was designed to detect a difference between groups in terms of 1 additional retrieved oocyte after the hCG trigger with a standard deviation of 3 retrieved oocytes. The power is set at 90%, along with a 2-sided 5% type I error rate. To account for a 20% dropout rate, the sample size of 480 was determined using PASS 15.0 (NCSS, LLC, Kaysville, Utah), in which 240 participants were in each group.

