### 2.11. Trial monitoring

A trial monitoring committee (TMC) has been established, including principal researchers in each reproductive center. The TMC is responsible for data monitoring, adverse event assessment, regulation of the study process monthly, the interim analysis, and the decision on terminating the study or not.

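### The plan allows an efficacy stop at an interim look but keeps the full two-sided P < .05 for the final test, so the stated 5% type I error is not delivered

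*Protocol article*

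**What the plan says.** Among the conditions for terminating the trial, Section 2.5 lists: "The prespecified interim analysis finds the expected difference in efficacy between the groups". No number is attached to the expected difference there, and no timing or number of looks is given.

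Section 2.9.1.1 plans for "1 additional retrieved oocyte after the hCG trigger with a standard deviation of 3 retrieved oocytes" and adds: "The power is set at 90%, along with a 2-sided 5% type I error rate". It continues: "To account for a 20% dropout rate, the sample size of 480 was determined using PASS 15.0". Section 2.9.2 states that a two-sided P < .05 "is considered statistically significant with a confidence interval of 95" per cent; it makes no allowance for an earlier look. The Discussion (Section 3) describes the 90% power as applying to a difference of 3 oocytes, not 1.

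Section 2.11 describes a trial monitoring committee (TMC), "including principal researchers in each reproductive center", and makes it responsible for "the interim analysis, and the decision on terminating the study or not". Section 2.6 says: "The outcome assessment and data analysis will also be conducted in blinding", and places the final breaking of the blind after the trial has ended. Section 2.12 routes serious adverse events to the same TMC and couples them with a break of the blind.

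**The concern.** If a trial can be declared successful at an interim look, that look uses part of the type I error. The final test must then be made at a smaller level, or the total exceeds the stated figure. Here both the rule and the final level are stated, and they do not fit together. The criterion is also worded as a difference that is found, not as a significance boundary. Read literally, it is weak early in the trial, when an observed difference of 1 oocyte can easily arise by chance, and a trial that stops on it will tend to overstate the effect.

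A second issue is who handles the interim. Judging whether EZTG shows an advantage needs a between-group comparison and its direction. Principal researchers of the participating centres sit on the committee responsible for that step, while rFSH dosing in those centres is individualised (Section 2.7.3). If comparative results reached treating staff, they could influence the primary outcome.

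**Working it through.** **Inputs.** Difference 1 oocyte, SD 3, two-sided 5%, 90% power, 20% dropout, 480 in total (Section 2.9.1.1); 1:1 allocation (Section 2.6); final level .05 (Section 2.9.2). Timing and number of looks are assumptions.

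**1. The plan's own figure.** n per arm = 2 × 3² × (1.960 + 1.282)² / 1² = 189.1, so 190. Dividing by 0.8 gives 237.5, so 238 per arm and 476 in total. The t-based version gives 191, then 239 per arm and 478 in total. The stated 480 is reproduced by single-look formulas at the full 5%. With 240 × 0.8 = 192 evaluable per arm, single-look power is 90.4%.

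**2. Overall error with one interim.** Under no effect, the interim and final statistics Z1 and Z2 are bivariate normal with correlation √t, where t is the information fraction. Overall error = P(stop at interim) + P(no stop and |Z2| > 1.96).

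- Reading A: stop if the interim two-sided P < .05.
- Reading B: stop if the observed difference favours EZTG by at least 1 oocyte. The threshold is c = 1 / (3 × √(2/n₁)), with n₁ evaluable per arm at the look.

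Reading B, worked at t = 0.5: n₁ = 96, SE = 3 × √(2/96) = 0.433, c = 2.31. P(stop) = 1.05%, P(no stop, final significant) = 4.53%, total 5.6%. At t = 0.25: n₁ = 48, c = 1.63, and 5.12% + 4.25% = 9.4%.

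| Information at the look | Reading A | Reading B, 192 per arm | Reading B, 240 per arm |
|---|---|---|---|
| 25% | 9.1% | 9.4% | 7.8% |
| 33% | 8.8% | 7.3% | 6.3% |
| 50% | 8.3% | 5.6% | 5.2% |
| 67% | 7.7% | 5.1% | 5.0% |
| 75% | 7.3% | 5.0% (5.02%) | 5.0% |

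With equally spaced looks, all at P < .05, simulation gives 10.7%, 12.6% and 14.2% for 3, 4 and 5 looks in total.

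**3. Which difference is expected?** A design for 3 oocytes with SD 3 would need 2 × 9 × (1.960 + 1.282)² / 9 = 21.0, so 22 per arm. The Discussion's figure therefore does not match the sample size of 480, but it leaves two values in the article for the same criterion.

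**4. Overestimation on stopping.** If the true effect is 1 oocyte, reading B at half information stops 50% of trials. The mean estimate among those is 1 + 0.433 × 0.798 = 1.35 oocytes.

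**5. A boundary that fits.** One look at t = 0.5, with nominal two-sided levels 0.00305 (z = 2.963) at the interim and 0.049 (z = 1.969) at the end, gives an overall error of 0.0500. Power with 192 evaluable per arm is 90.33%, against 90.42% for the single look. Stopping then needs an observed difference of about 2.963 × 0.433 = 1.28 oocytes. If the true effect is 1 oocyte, about 26% of trials stop, with a mean estimate of 1.54 among them.

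**The case against.** The strongest reply is that this is a condensed article. The interim is called prespecified, so timing and boundary may well be in a fuller plan, and their absence here is not a finding. That is accepted. It does not dispose of the point, because the article itself fixes the final level at the full .05 and the sample size as a single look. A boundary held elsewhere cannot restore 5% while that final level stands. A very strict boundary would make the excess trivial, however: P < 0.001 at half information followed by .05 gives 5.02%.

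Three stronger readings are tempting, and the documents do not support them.

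- A reader might take the criterion to mean exactly 1 oocyte in either direction, which gives 6.1% at half and 13.7% at a quarter of the information. The article describes a superiority trial seeking additional oocytes, so counting stops that favour placebo overstates the error, and no number is attached to the criterion in Section 2.5.
- A reader might infer that the TMC is made up solely of recruiting investigators. Section 2.11 says only that it includes the centres' principal researchers; Section 2.2 assigns recruitment to clinicians of those centres.
- A reader might infer that the blind is broken at the interim and that TMC members then dose or score symptoms knowing the results. No section says so, and an analysis by coded arm is compatible with Section 2.6. What remains is a tension: coded arms protect less when the same committee receives serious adverse events with the blind broken (Section 2.12).

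**Conclusion.** The point holds on stated text: an efficacy stop, a single-look sample size and an unadjusted final level cannot together give a two-sided 5% error. The size cannot be fixed from the article. For one look it runs from negligible (5.02%, a late look under the 1-oocyte reading) to nearly double (9.4%, an early look under the same reading); if the interim is tested at P < .05 it is 7.3% to 9.1%. These figures assume normal test statistics, SD 3 and, for the 1-oocyte reading, 192 evaluable per arm.

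The criterion is also ambiguous between 1 and 3 oocytes. The composition and duties of the TMC are hard to reconcile with Section 2.6, but the article does not show that the blind is lost.

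**What to change.** Replace the efficacy criterion in Section 2.5 with an alpha-spending boundary, and match the final level in Section 2.9.2. One example is a single look at 50% of primary-outcome data, stopping for efficacy only if two-sided P < 0.0031 (0.00305 before rounding), with the final test at 0.049. N stays 480 and power falls by about 0.1 percentage point. A classical O'Brien-Fleming pair, 0.0052 and 0.0480, is an equally valid choice, with power 90.2% at 192 evaluable per arm. Alternatively, delete the efficacy interim and keep P < .05. Correct the Discussion so that the design difference agrees with Section 2.9.1.1.

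If the interim is kept, state in Section 2.11 that site researchers on the TMC receive only a recommendation to continue or stop, from a statistician who does not recruit, treat or assess. If the statisticians who supply the random number tables take this on, Section 2.6 must be amended, since it now gives them no other part in the study.

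The boundary makes early stops rarer (about 26% instead of 50% if the true effect is 1 oocyte) but does not remove overestimation in the trials that stop. An estimate after early stopping should be adjusted, or reported with that caveat. The cost is protocol wording and naming the person who holds the unblinded comparison.
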